#### *Safety assessment*

|                          |   |   |   |   |   |   |
|--------------------------|---|---|---|---|---|---|
| Routine blood tests      | × | × | × | × | × | × |
| Routine urine tests      | × | × | × | × | × | × |
| Liver functions tests    | × | × | × | × | × | × |
| Renal functions tests    | × | × | × | × | × | × |
| Blood glucose and lipids | × | × | × | × | × | × |
| Bone mineral density     | × |   |   | × |   | × |
| Hepatitis B virus        | × |   |   | × |   | × |

#### *Adherence lab assessment*

|                          |  |   |   |   |   |   |
|--------------------------|--|---|---|---|---|---|
| Blood drug level testing |  | × | × | × | × | × |
|--------------------------|--|---|---|---|---|---|

Abbreviations: FU, follow-up; m, month(s); d, day. a Items that PrEP nonusers need to complete. # PrEP nonusers do not need to attend this follow-up visit. a Anyone who screens positive for HIV will have the results confirmed by western blotting. b Anyone who screens negative for HIV will have the results confirmed by HIV RNA pooling PCR test. c Anyone who tests positive for HIV will have their samples further tested for HIV resistance and viral load.

### **Laboratory Procedures**

As summarized in Table 3, during each clinical visit, participants will be asked to provide blood and urine specimens for monitoring of HIV infection, STIs, and objective measures for adherence and safety of PrEP use. Analysis of blood TDF/FTC concentrations will be performed in the Key Laboratory of AIDS Immunology of National Health Commission, Department of Laboratory Medicine, The First Affiliated Hospital, China Medical University, in Shenyang, China. All other testing will be conducted by nationally certified laboratories, located at each research center. Dry blood spots and serum samples will be collected at every visit for TDF/FTC drug level testing.

If a participant is found to have seroconverted to HIV, his participation in the study will be terminated immediately and he will be called for a final visit. At the final visit, study staff will collect unused pills, conduct resistance and viral load testing, and provide referrals to an HIV clinic for treatment. The study staff will report each case of seroconversion to the sponsor.

**Table 3 Laboratory Parameters**

| Laboratory Parameter | Test |
|-----------------------------|-------------|
|-----------------------------|-------------|

|                          |                                                                                                                                                                                                                                                                                                                        |
|--------------------------|------------------------------------------------------------------------------------------------------------------------------------------------------------------------------------------------------------------------------------------------------------------------------------------------------------------------|
| HIV                      | HIV serostatus is evaluated by ELISA (InTec Products Company, Xiamen, China), and confirmed with an HIV-1/2 western blot (HIV Blot 2.2 WBTM, Genelabs Diagnostics, Singapore). The results of anyone who screens negative for HIV will be confirmed by HIV RNA pooling PCR test (COBAS AmpliPrep /COBAS TaqMan, Roche) |
| HIV resistance           | RNA sequencing                                                                                                                                                                                                                                                                                                         |
| HIV viral load testing   | COBAS AmpliPrep /COBAS TaqManv (Roche)                                                                                                                                                                                                                                                                                 |
| Syphilis                 | RPR (Shanghai Rongsheng, Shanghai, China) and TPPA (Fujirebio Inc, Tokyo, Japan)                                                                                                                                                                                                                                       |
| Hepatitis B              | HBsAg (Vitros 5600)                                                                                                                                                                                                                                                                                                    |
| HSV-2                    | IgM-HSV-2, IgG-HSV-2 (Beier Bioengineering, Beijing, China)                                                                                                                                                                                                                                                            |
| Biochemistry             | AST, ALT, total bilirubin, creatinine, creatinine clearance, serum phosphate, blood glucose, and lipids (Roche)                                                                                                                                                                                                        |
| Routine blood tests      | Full blood count: hemoglobin, leucocytes, platelets; differential count: absolute neutrophil count, absolute lymphocyte count (Mindray BC-5800)                                                                                                                                                                        |
| Routine urine tests      | Proteinuria (Mindray EH-2080)                                                                                                                                                                                                                                                                                          |
| Blood drug level testing | LC-MS (AB SCIEX API 6500+)                                                                                                                                                                                                                                                                                             |

---

Abbreviations: ELISA, enzyme-linked immunosorbent assay; RPR, rapid plasma reagin; TPPA, *Treponema pallidum* particle agglutination assay; HSV-2, Herpes simplex virus 2; HBsAg, Hepatitis B surface antigen; AST, aspartate transferase; ALT, alanine transferase; LC-MS, Liquid chromatography-mass spectrometry.

### **Safety assurance**

All PrEP users should receive safety assurance at each follow-up. Safety of TDF/FTC will be monitored by laboratory ratings, based on vital signs and adverse events recorded on a paper case report form at each clinic visit, and the results of causal association and severity assessment will be independently evaluated by two physicians. Any reported adverse events will be clinically tracked until they are restored or stabilized. Serious adverse events are life-threatening events, including HIV

seroconversions that must be reported to the sponsor within one business day, and the lead ethics committee within 72 h.

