#### **1. The real-life effectiveness of daily or event-driven PrEP use:**

— HIV incidence among individuals using different PrEP regimens, compared with that of non-PrEP users randomly selected by propensity score from local expanding cohort studies of

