### **3. Safety and tolerability:**

- Rate of side effects or adverse events related to PrEP use
- Rate of adverse events related to discontinuation of PrEP or switching PrEP regimens

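### The protocol counts only life-threatening events and HIV seroconversion as serious, so other serious harms have no expedited reporting route

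*Protocol*

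**What the plan says.** The Safety assurance section of the protocol defines seriousness in one sentence. It begins "Serious adverse events are life-threatening events, including HIV" and continues "seroconversions that must be reported to the sponsor within one business day, and the lead ethics committee within 72 h". No other criterion for seriousness appears in the protocol, and no other expedited deadline for an adverse event.

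The same section describes how adverse events in general are handled. It covers PrEP users ("All PrEP users should receive safety assurance at each follow-up"). It says of assessment that "the results of causal association and severity assessment will be independently evaluated by two physicians", and of follow-up that "Any reported adverse events will be clinically tracked until they are restored or stabilized". Neither statement carries a reporting time.

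Three other places bear on the point:

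- **Table 2, safety assessment:** kidney and liver function tests are scheduled at screening and at months 1, 3, 6, 9 and 12, and bone mineral density at screening and months 6 and 12.
- **Laboratory Procedures:** a seroconversion ends participation, and staff report each case to the sponsor.
- **Table 4:** the first effectiveness end point is "HIV incidence among individuals using different PrEP regimens", compared with nonusers. The two safety end points are "Rate of side effects or adverse events related to PrEP use" and "Rate of adverse events related to discontinuation of PrEP or switching PrEP regimens".

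**The concern.** Seriousness decides which events the sponsor and the ethics committee hear about at once. A rule that stops at threat to life leaves out hospital admission, lasting disability and other medically important events. Death is at best implied. The harms this protocol looks for, in kidney, liver and bone, can be grave without being immediately life-threatening.

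At stake is timely oversight. About 1000 HIV-negative men are to take the drug for up to 12 months, and safety and tolerability is one of the four stated objectives. A cluster of admissions for kidney injury at one centre could build up with no rule obliging anyone to tell the sponsor before routine data review.

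A smaller matter is attached. By naming seroconversion a serious adverse event, the protocol places its effectiveness outcome among the safety events as well, and gives no rule for keeping the two apart in tabulation.

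**Working it through.** No arithmetic applies. The protocol states no event rates, and its sample size is not based on a power calculation. The check is a reading of the rule against the events it must sort.

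**Step 1: which events have a deadline?** The sentence can be read in two ways. Under reading A, the two deadlines apply to every serious adverse event. Under reading B, the clause on reporting attaches only to seroconversions.

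| Event in a PrEP user | Serious under the rule? | Deadline, reading A | Deadline, reading B |
|---|---|---|---|
| HIV seroconversion | Yes, named | 1 business day / 72 h | 1 business day / 72 h |
| Other life-threatening event | Yes | 1 business day / 72 h | None stated |
| Admission for kidney injury, not life-threatening | No | None | None |
| Disabling fracture, not life-threatening | No | None | None |

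The last two rows come out the same under both readings, so the gap does not depend on how the sentence is parsed. Reading B only makes it wider.

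**Step 2: does other text fill the gap?** The two physicians judge causality and severity. Severity grades intensity and is not seriousness, so their review does not start a reporting clock. Follow-up until recovery or stabilisation is clinical tracking, not notification. The report to the sponsor under Laboratory Procedures concerns seroconversions only.

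**Step 3: are the omitted events lost?** No. Adverse events are documented at each clinic visit (Study visits), extracted from medical records by trained staff (Data collection and quality assurance), assessed and followed. Safety end point 1 in Table 4 counts events related to PrEP whether or not they are serious. An omitted event lacks a serious label and a deadline, but it stays in the data.

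**Step 4: where does seroconversion go?**

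- It is counted under effectiveness through HIV incidence.
- It is a serious adverse event by the Safety assurance sentence.
- It enters safety end point 1 only if judged related to PrEP.
- It could enter safety end point 2 if that end point means events leading to discontinuation, because seroconversion ends participation.
- No passage says to exclude it or to show it separately.

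**The case against.** The strongest reply is that nothing the protocol plans to estimate is affected. Table 4 contains no rate of serious adverse events, so no such rate can be too low or can mix failed prevention with toxicity. Admissions and fractures are still recorded, assessed and tracked. This stands: a reader might infer that serious harms are under-counted in the end points, and the documents do not support that.

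The reply continues that expediting seroconversions is sensible, since each one ends participation and triggers resistance testing, and resistance among seroconverters is itself an end point. This also stands. Prompt reporting of seroconversion is not the fault. HIV incidence is analysed as its own end point, so the safety label does not alter the effectiveness result. What remains is the absence of a rule for tabulating these events apart from other adverse events.

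A reader might also infer that safety end point 2 measures the wrong direction, counting events that follow stopping instead of events that cause it. The wording can naturally mean events leading to stopping or switching, and the adherence list in Table 4 already records the reasons for switching regimens. The wording is ambiguous and no more than that.

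Finally, a reader might suppose that seroconversions would make up most of the serious events. That would need an HIV incidence, an effectiveness figure and a count of other serious events, none of which the protocol gives.

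None of this answers the central point. The protocol states a seriousness rule, and the rule leaves non-life-threatening serious harms without an expedited route. This is not detail that a statistical analysis plan would normally supply, because seriousness criteria and reporting deadlines belong in the protocol.

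**Conclusion.** The point holds as a fault in safety reporting. The stated definition is narrower than the harms the study sets out to monitor, and under either reading of the sentence a serious event that is not life-threatening has no deadline. The consequence is missing serious classification and possibly late notification for PrEP users. It does not bias any end point in Table 4. The number of events affected cannot be estimated from the document.

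The double role of seroconversion is a secondary matter of tabulation, and the wording of safety end point 2 is an optional clarification.

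The conclusion assumes that the protocol text is the operative rule. A separate safety manual could widen the definition, but the protocol refers to none. The change is worth making because it is cheap and safety is a stated objective.

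**What to change.** 1. In Safety assurance, define a serious adverse event as one that is fatal, is life-threatening, requires or prolongs a hospital stay, causes lasting disability, or is otherwise medically important. State in a separate sentence that the existing deadlines to the sponsor and the lead ethics committee apply to all such events, which also removes the ambiguity between the two readings.
2. Keep seroconversion on the same deadlines, named as a separately reported event, and say that it is tabulated apart from other adverse events. It is already the effectiveness outcome and already goes to the sponsor under Laboratory Procedures.
3. Optionally, reword safety end point 2 in Table 4 as the rate of PrEP discontinuation or regimen switch because of an adverse event.

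The cost is a change of wording in two places, matching instructions for the case report form, and a few more expedited reports. No dose, visit or treatment rule changes.

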### **Data collection and quality assurance**

The results from both types of data collection will be triangulated to assess various end points. A specialized platform for questionnaire collection will be used to collect self-administered, structured questionnaires to assess socio-demographic information, perceived skills, willingness, impact of PrEP use on behaviors and mental status, self-reported adherence, and side effects. All examination results will be interpreted and organized into structured data by professional physicians. For unstructured data, such as medical records and drug release records, core information on adverse events, medications, and tablet counts will be extracted by trained staff. Over the course of the study, we will establish and strictly operate a system of quality control to ensure the integrity, validity, and authenticity of data (Fig 2). Besides, data inspection companies are employed as independent from investigators and the sponsor for auditing trial conduct.

### **Study end points**

As shown in Table 4, primary and secondary end points will be pursued to determine the feasibility and operationalization of PrEP implementation in China.

Adherence to PrEP will be measured from different perspectives: drug concentration testing, self-reported adherence via questionnaires and weekly messages, self-report to clinician, dispensing and return records, and drug level assessment.

**Table 4 End points of the *CROPrEP* project**

---

#### **1. The real-life effectiveness of daily or event-driven PrEP use:**

— HIV incidence among individuals using different PrEP regimens, compared with that of non-PrEP users randomly selected by propensity score from local expanding cohort studies of

## HIV-negative MSM

- The rate of viral genotype resistance among individuals who seroconvert to HIV during the study period

### **2. Adherence to PrEP:**

- Number, proportion and patterns of prescribed doses taken and missed according to self-reported adherence via online questionnaires and weekly messages, reported pill use, and pill counts
- Testing of FTC/TDF drug concentration in blood samples
- Percentage of participants who switch regimens and their reasons

### **3. Safety and tolerability:**

- Rate of side effects or adverse events related to PrEP use
- Rate of adverse events related to discontinuation of PrEP or switching PrEP regimens

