**Table 1 Inclusion and exclusion criteria for participants in the CROPrEP project**

**Inclusion criteria**

- Aged 18–65 years old\*
- Born to male sex\*
- Test results demonstrate HIV negative\*
- Had sex with a man in the last 6 months\*
- **Behavioral eligibility criteria**\*

Participants of male sex at birth and who have sex with men, reporting at least one criterion associated with high risk for HIV infection in the 6 months prior to enrolment as follows:

- Unprotected (condom-less) receptive anal intercourse with male partners
- More than two male partners (regardless of condom use and HIV serostatus)
- Reported STI, such as syphilis, HSV-2, gonorrhea, chlamydia, chancroid, or lymphogranuloma venereum
- Reported a history of post-exposure prophylaxis

Note: Individuals in a monogamous relationship with an HIV-1 seronegative partner or a virologically suppressed HIV-1+ partner for > 1 year will not be eligible for participation.

- Through comprehensive physical examination, including routine urine examinations, hepatic and renal function tests, blood glucose and lipids, and BMD; no serious liver or kidney dysfunction and negative for HBs antigen, without serology indicating osteoporosis, and other indicators are normal
- Able and being willing to sign written informed consent and participate in the study as procedures require\*
- Chinese citizens\*

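### Table 4's safety end points are attributed-event rates only, so gradual change in creatinine clearance or bone density is captured by no end point, and no untreated laboratory data are scheduled to check the attribution

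*Protocol*

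**What the plan says.** The protocol lists safety and tolerability as one of four objectives. Table 4, end point 3, gives it two measures:

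- "Rate of side effects or adverse events related to PrEP use"
- "Rate of adverse events related to discontinuation of PrEP or switching PrEP regimens"

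The Safety assurance section describes how events are evaluated: "Safety of TDF/FTC will be monitored by laboratory ratings, based on vital signs and adverse events recorded on a paper case report form", and "causal association and severity assessment will be independently evaluated by two physicians". It also says who is covered: "All PrEP users should receive safety assurance at each follow-up".

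Table 2 schedules renal function tests at screening and months 1, 3, 6, 9 and 12, and bone mineral density at screening and months 6 and 12. Table 3 lists creatinine, creatinine clearance and serum phosphate among the biochemistry tests. The Study visits section says that biological indices are monitored at clinic visits for toxicity due to PrEP.

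In Table 4, the comparison with nonusers is attached to HIV incidence only. In Table 2, the mark for items that nonusers complete is on informed consent and HIV/STI testing. It is not on the safety panel or the adverse event row.

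**The concern.** Both safety measures depend on someone attributing an event to PrEP, or to stopping or switching it. Table 4 asks for no rate of adverse events regardless of cause, and no measured quantity such as change in creatinine clearance or bone density. A slow decline that nobody records as a related event would therefore leave both end points unchanged, although the study pays for repeated measurements that could show it.

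The attribution also has nothing to be checked against. The study is open, regimens are self-chosen, and no safety laboratory tests are scheduled for nonusers.

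The second measure appears to be the wrong way round for tolerability. The usual question is how many men stopped or changed treatment because of an event. The line as written asks how many events were related to stopping or changing.

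**Working it through.** The protocol gives no planned rate, standard deviation, alpha or power for safety, so there is no figure to reproduce. The check is to trace each kind of safety information to the end point that would use it.

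**1. Amount of data.** Inputs are 1023 PrEP users (Overview of study design), six renal time points and three bone density time points (Table 2). I assume full attendance, and that creatinine clearance (Table 3) is part of the renal function tests in Table 2.

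- Renal panels: 1023 × 6 = 6138, of which 1023 × 5 = 5115 are after screening.
- Bone density: 1023 × 3 = 3069, of which 1023 × 2 = 2046 are after screening.

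**2. Route from measurement to end point.**

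| Information | Collected? | Enters Table 4, end point 3? |
|---|---|---|
| Renal or bone abnormality recorded as an adverse event and judged related | Yes | Yes, first line |
| The same abnormality judged unrelated to PrEP | Yes | Not in the first line |
| Change that is never recorded as an event | Yes | No |
| Average within-person change from screening | Can be derived | Not named |
| Adverse events regardless of cause | Yes | Not named |

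If creatinine clearance drifted down across the cohort and no man's value was recorded as a related event, both safety end points would be unaffected.

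**3. Is this only analysis detail?** A protocol may leave the method for a listed end point to the SAP. Here Table 4 itself fixes the list, and elsewhere in that table measured quantities are named: drug concentration under end point 2, and changes in partner numbers, condom use and syphilis incidence under the final end point. The safety entry alone omits the quantities scheduled for it.

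**4. Untreated reference.** The laboratory entry criterion in Table 1 and the safety panel in Table 2 lack the nonuser mark, and Safety assurance refers to PrEP users. No untreated renal or bone data are therefore planned. For adverse events the text is unclear. Study visits introduces the nonusers' quarterly visits and then says that adverse events are documented at each clinic visit, while Table 2 does not mark that row for nonusers. This matters because relatedness to PrEP has no meaning in a man who takes none. Only an all-cause rate could be set beside nonusers.

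**5. The second line.** Take a man who stops PrEP because of nausea. The nausea can count in the first line, as an event related to use. On a literal reading of the second line, neither his stopping nor the nausea counts, because the event was not related to stopping. Table 4, end point 2, already asks how many men switch regimen and why, so switching because of an event is recoverable there. Discontinuation because of an event has no such entry.

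**The case against.** The strongest reply is that the laboratory data are not idle. Safety assurance makes laboratory ratings part of safety monitoring, and Study visits ties the indices to PrEP toxicity, so a renal or bone abnormality judged related does enter the first end point. That stands. A reader might infer that the creatinine clearance and bone density data serve no end point at all, and the documents do not support that. What has no end point is change that does not become a related event.

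A second reply is that nothing bars a descriptive summary of laboratory change, overall or by regimen, and that an SAP not shown may contain one. That also stands. It would be wrong to say that the trial cannot report how much these measures changed. The point is only that the protocol's own end point list does not ask for it.

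Third, attribution by physicians is not the only route. Side effects are also self-reported by questionnaire, and nothing says that those reports must pass the two physicians. No text states what the physicians know about treatment either. That they know each man takes PrEP is a reasonable inference from an open study, not a stated fact.

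Fourth, entry requires men to be "without serology indicating osteoporosis, and other indicators are normal", which tempts a reader to calculate how many would leave the normal range by chance and to call that a bias. The documents do not support the step: no text makes an out-of-range value an adverse event, so such a count would not measure error in the end point.

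Finally, the second line can be read loosely as events associated with stopping or switching. That reading is possible, which is why the line needs clearer wording.

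**Conclusion.** The point holds in a limited form. Both safety end points are attributed-event rates. Creatinine clearance and bone density count only when an abnormality is recorded as a PrEP-related adverse event. Gradual or sub-threshold change falls outside Table 4, and no untreated safety laboratory data are scheduled to check the attribution. The second line, taken literally, does not measure discontinuation because of an event.

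The size is the quantity of data with no named quantitative use: up to 5115 post-screening renal panels and 2046 post-screening bone density measurements. The documents give no basis for estimating a bias in either direction. The conclusion rests on reading the nonuser mark in Table 2 as the asterisk on consent and HIV/STI testing; its footnote symbol is unclear in the text available. This is a cheap improvement to a demonstration project, not a flaw that undermines it.

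**What to change.** In Table 4, end point 3:

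1. Report all adverse events regardless of relatedness, with the PrEP-related rate as a subset.
2. Add within-person change from screening in creatinine clearance (each follow-up visit) and bone density (months 6 and 12), overall and descriptively by regimen and by pills taken. State that regimen is self-chosen and can be switched, so the regimen contrast is confounded, and that there is no untreated comparison for these measures. The edit does not create one.
3. Reword the second line as the proportion of men who discontinue or switch PrEP because of an adverse event.

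Separately, reconcile the Study visits text on documenting adverse events at each clinic visit with Table 2, where that row is not marked for nonusers.

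No visit or test is added. The cost is a few lines of protocol text, a little more analysis, and a reported adverse event rate higher than the related rate alone.
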